### Data analysis

We will build a standard regression model to estimate the relation between healthcare utilisation and key variables capturing the configuration of liaison psychiatry services. The dependent variable in this model will therefore be the total costs of any identified healthcare utilisation derived from factors such as inpatient days, readmission rates, ED attendances and GP visits combined with reference costs. These reference costs will be valued using national sources, including the Department of Health Reference Costs^38^ and Personal Social Services Research Institute Costs for Health and Social Care.^39^ Where these are not available, local costs will be assigned. We will choose the most appropriate base year for the analysis and adjust appropriately for the effects of inflation across years. The quantum of the liaison psychiatry service provision will be captured by already collected data related to structure and process, for example, staffing levels and contact time after referral. We will adjust for referral indication bias, either by matching for covariates or by propensity scoring.

Sample size is difficult to estimate because we have so little available data on outcomes for different service types and different patient groups. Suppose we identify six main service configurations and recruit two liaison psychiatry services for each (total n=12). For less common conditions we might expect to see one referral per week per service=100 in total in the year. For more common conditions we might perhaps see one referral per day or 600–800 in the year. These numbers will allow us to estimate the costs and cost-effectiveness of liaison psychiatry services with substantially greater precision than has been achieved to date, for example, by the RAID evaluation.

The way in which components of general hospital, general mental health and liaison psychiatry services interact with each other is complex and a key part of the project will be to determine how to capture this complexity into a set of measures for inclusion in the model.

We ([name]) will carry out exploratory incremental cost-effectiveness analyses using decision analysis modelling. The model will rely on the retrospectively estimated healthcare costs of alternative care pathways and the characteristics at hospital, service and patient level. Given the nature of the data available, the absence of measures such as Quality of Life measures and the heterogeneous nature of the population, we will explore the use of a range of variables to assess effectiveness and evaluate the costs per length of stay, per re-admission and per life years lost. The health economics analyses will be informed by earlier work packages in the Liaison psychiatry—measurement and evaluation of service types, referral patterns and outcomes (LP-MAESTRO) project. However, we will also follow the guidance from the National Institute for Clinical Excellence (NICE) for methods for technology appraisal.^40^ While it is clear that some aspects of an exploratory model (or indeed models) may be specified in advance, for example, the perspective of the economic evaluation which will be the health service provider and the comparator which will be usual care, other aspects will be dependent on the shape of the services and the populations they engage with.

At this point we are unable to specify the time horizon of the decision analysis model evaluating the long-term cost-effectiveness of liaison psychiatry services. We will look to a long-term model and use NICE recommended discount rates for costs. The model itself is likely to be Markov or semi-Markov. Sensitivity analyses will be undertaken in line with those recommended for this type of modelling.^41^ Presentation of the analysis or analyses will include incremental cost-effectiveness ratios, cost-effectiveness acceptability curves and net monetary benefit estimates. In addition, we will undertake a value of information analysis.^42^

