First, cost pressures in the NHS and the emergence of commissioning led by Clinical Commissioning Groups will continue to lead to re-profiling of services and especially attempts to reduce unnecessary hospital costs. Work on developing and implementing risk stratification models is an illustration and it is interesting that many of these models identify comorbid physical and mental health problems as a risk, both for increased healthcare costs and for the main driver of such costs which is unscheduled hospital admission. A study from Birmingham describing the evaluation of a rapid assessment, intervention and discharge service (previously widely known by the acronym RAID) was widely promoted and is leading to commissioning of similar services that will be hoped to reduce costs.^21 22^ There were however substantial problems with that evaluation: it reported only on the first 9 months of delivery of a new service; it used a simple before and after design; it compared outcomes between referred and a matched group of non-referred patients in only 79 cases with minimal matching that cannot have dealt with indication bias and much of the benefit was attributed to the so-called indirect liaison cases who were in fact not seen by the service but assumed to benefit by its existence in the hospital. Other ‘RAID’-like services have also reported large savings in cost or reductions in hospital use following implementation.^23 24^ So a key answer to the question of why this research is needed now is the pressing need to confirm or refute the very striking claims made for similar services, but using larger numbers and more robust research methods.

Second, there is a danger of losing sight of the other main functions of liaison psychiatry services, which do not exist only to reduce costs in the general hospital but which are aimed at improving the well-being of patients, some of whom are being treated entirely or appropriately in the general hospital and happen to need mental health service input because of the complexity of their problems.

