To address the first limitation, clinical databases controlled by the mental health trusts that provide liaison psychiatry services will be used. Such databases contain patient data relating to care provided by liaison psychiatry services and can be used in conjunction with HES data to determine whether a patient was referred to a liaison psychiatry service during a hospital admission. The main challenges with the use of such databases are data quality and the heterogeneous processes by which data access is negotiated and administered within different organisations.

To address the second and third limitation, data relating to primary care is required for each patient. Although the Clinical Practice Research Datalink database^31^ is widely used for primary care research in the UK, it has a major drawback for this study—limited numbers and geographical coverage of participating primary care organisations at the time of study design. Instead ResearchOne,^32^ a research database controlled by The Phoenix Partnership (TPP), will be used. ResearchOne contains patient data relating to primary care provided by organisations using the SystmOne clinical information system.^33^ SystmOne (34%) and EMIS^34^ (56%) are the most prevalent clinical information systems used by organisations in general practice.^35^ Therefore, many of the patients with episodes in the HES data can be expected to have data relating to their primary care collected by organisations that use SystmOne. ResearchOne contains data for a subset of these patients—patients who: (1) are registered to organisations that use SystmOne and have opted-in to participation in ResearchOne and (2) have not individually opted-out of participation in ResearchOne. The main challenge with the use of ResearchOne is the inability to determine a priori the numbers and geographical coverage of organisations that provide primary care to patients attending the hospitals chosen for the study, and the resultant ability to match HES data to corresponding ResearchOne data for each patient.

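### The sample-size totals fit one configuration of two services, not the twelve services stated, and leave out linkage loss; the claimed precision gain is unsupported for less common conditions within a single configuration

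*Protocol article*

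**What the plan says.** All references are to the Protocol article.

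- **Data analysis**, the scenario: "Suppose we identify six main service configurations and recruit two liaison psychiatry services for each (total n=12".
- **Data analysis**, the counts: "For less common conditions we might expect to see one referral per week per service=100 in total in the year", followed by "For more common conditions we might perhaps see one referral per day or 600–800 in the year".
- **Data analysis**, the conclusion: these numbers are said to allow costs and cost-effectiveness to be estimated "with substantially greater precision than has been achieved to date, for example, by the RAID evaluation".
- **Introduction**: the RAID evaluation is criticised for comparing referred patients with a "matched group of non-referred patients in only 79 cases".
- **Study design** and **Data sources**: both control groups are matched on hospital and primary care data. The primary care data come from ResearchOne, which covers only patients who "are registered to organisations that use SystmOne and have opted-in to participation in ResearchOne" and who have not opted out individually. SystmOne's share of general practice organisations is given as 34%. The section concedes that the linkage yield cannot be known beforehand.
- **Aims and objectives**: outcomes for certain marker conditions are to be compared between service configurations.

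**The concern.** The first count is labelled as a total directly after the number of services is set at 12, yet it is about one sixth of what that number and the weekly rate produce. A reader cannot tell whether 100 and 600–800 describe the whole study or one configuration. The precision claim refers back to exactly these numbers.

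The counts also stop at referral. A referred patient without a ResearchOne record cannot be matched as the design requires, so the analysable number is smaller, and the paragraph applies neither a reduction nor a range.

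At stake is what the study can be expected to say about a less common condition in one type of service. That is a level at which comparisons are planned, and the comparator there is a study faulted for having only 79 cases.

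**Working it through.** **Inputs.** 6 configurations × 2 services = 12 services; one referral per week per service (less common conditions); one referral per day (commoner conditions; the text does not repeat the per-service qualifier, so this is read as per service); a one-year index period; 79 RAID cases; SystmOne share 34%.

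**Step 1: reproduce the printed counts.** Count = rate × weeks or days × number of services.

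| Services | Weekly rate | Daily rate |
|---|---|---|
| 1 | 52 | 365 |
| 2 | 104 | 730 |
| 12 | 624 | 4,380 |
| Printed | 100 | 600–800 |

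Only the two-service row fits both printed figures. Rounding does not close the gap: a 50-week year with 12 services still gives 600, and counting weekdays only gives 12 × 260 = 3,120. The printed weekly figure is short of the twelve-service total by a factor of 624 / 100 = 6.2.

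**Step 2: the precision claim on the printed figure, with no loss.** With equal variance and the same matching ratio, and patients treated as independent, the ratio of standard errors to that of the RAID evaluation is √(79 / n). For n = 100 it is √(79 / 100) = 0.89, a standard error 11% smaller.

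**Step 3: allow for linkage.** Linked n = referrals × linkage fraction. The documents give no linkage fraction. I take 34% as an illustration, with half (17%) and double (68%) as an assumed range. Each cell shows linked n and, in brackets, √(79 / n).

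| Linkage | Less common, one configuration (104) | Less common, 12 services (624) | Common, one configuration (730) | Common, 12 services (4,380) |
|---|---|---|---|---|
| 100% | 104 (0.87) | 624 (0.36) | 730 (0.33) | 4,380 (0.13) |
| 68% | 71 (1.06) | 424 (0.43) | 496 (0.40) | 2,978 (0.16) |
| 34% | 35 (1.49) | 212 (0.61) | 248 (0.56) | 1,489 (0.23) |
| 17% | 18 (2.11) | 106 (0.86) | 124 (0.80) | 745 (0.33) |

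**Step 4: break-even linkage.** The fraction at which linked n equals 79 is 79 / referrals:

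- Less common, one configuration: 79 / 104 = 76%.
- Less common, 12 services: 79 / 624 = 12.7%.
- Common, one configuration: 79 / 730 = 10.8%.
- Common, 12 services: 79 / 4,380 = 1.8%.

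**The case against.** The strongest reply is that correcting the total helps the study. Going from 100 to 624 raises the pooled number sixfold, and at 34% linkage 212 patients still give a clearly smaller standard error than 79 cases. A reader might infer that, because the printed total is wrong and linkage is ignored, the gain over the RAID evaluation fails for less common conditions altogether. The documents do not support that: pooled over 12 services, the advantage disappears only below 12.7% linkage.

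Other parts of the reply also stand:

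- The precision sentence speaks of liaison psychiatry services generally. It does not promise better precision for every condition in every configuration.
- The 79 cases are not described as a single condition, so setting one condition in one configuration against them is indicative only.
- A reader might take 34% as an upper limit on linkage. It is a national share of practice organisations, not of patients, and the services are sampled purposively, so local coverage may be higher or lower.
- The paragraph is openly tentative, and the Discussion warns that some subgroups may be too small for useful analysis.
- A reader might also infer that ED referrals and repeat referrals inflate the counts. The paragraph does not say whether they are included, so no size can be put on this.

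The reply does not rescue the count itself. Tentative wording makes the referral rate uncertain, not the multiplication, and the Discussion's caveat corrects neither the total nor the precision statement. This is also not detail left to a fuller document: the article prints a figure that disagrees with its own inputs and draws a conclusion from it.

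**Conclusion.** The concern holds in two parts of different strength.

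The arithmetic error is certain for the weekly count: the stated inputs give about 624, not 100. For the daily count it holds if the rate is per service (about 4,380, not 600–800), which is the natural reading because two services then reproduce both printed figures.

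The consequence for precision is conditional. At an assumed 34% linkage, a less common condition within one configuration has about 35 linked patients and a standard error about 1.5 times that of 79 cases. Even at twice that linkage the number, 71, stays below 79. Before any loss, 104 referrals reduce the standard error by only 13%, which is hard to call substantial. Pooled estimates, and common conditions even within one configuration, keep the gain throughout the 17–68% range shown, although it is modest at 17% for less common conditions pooled (0.86) and for common conditions in one configuration (0.80).

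These ratios rest on equal variance, an equal matching ratio and independent patients. The plan states no effect size, standard deviation or power, so nothing beyond relative precision can be checked.

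**What to change.** Rewrite the sample-size paragraph in Data analysis:

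1. Label 104 and 730 referrals a year as per configuration (two services), and give 624 and 4,380 as the totals over 12 services. State that the daily rate is per service.
2. Show expected linked numbers over a stated range of linkage fractions, and say that 34% is a national practice share that may not apply locally.
3. Limit the statement of substantially greater precision to analyses pooled over configurations or to common conditions.

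Comparisons of less common conditions between configurations can stay in the plan, as the aims intend. Restricting those conditions to pooled analysis would be a design preference and is not needed to correct the error.

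The cost is one paragraph. No additional patients, data or change of estimator is needed. The downside is that the stated per-configuration precision becomes less favourable.

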**Methods and analysis:**

The project will use three data sources: (1) Hospital Episode Statistics (HES), a database controlled by NHS Digital that contains patient data relating to emergency department (ED), inpatient and outpatient episodes at hospitals in England; (2) ResearchOne, a research database controlled by The Phoenix Partnership (TPP) that contains patient data relating to primary care provided by organisations using the SystmOne clinical information system and (3) clinical databases controlled by mental health trusts that contain patient data relating to care provided by liaison psychiatry services. We will link patient data from these sources to construct care pathways for patients who have been admitted to a particular hospital and determine those patients who have been seen by a liaison psychiatry service during their admission.

Patient care pathways will form the basis of a matched cohort design to test the effectiveness of liaison intervention. We will combine healthcare utilisation within care pathways using cost figures from national databases. We will compare the cost of each care pathway and the impact of a broad set of health-related outcomes to obtain preliminary estimates of cost-effectiveness for liaison psychiatry services. We will carry out an exploratory incremental cost-effectiveness analysis from a whole system perspective.

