Third, and related to the second point above, service commissioning and provision will benefit from a more standardised approach to service descriptors. Without more detailed knowledge about how to define the service being commissioned and how to evaluate whether it is working to remit and to improve Health-Related Quality of Life for patients, there is a risk of enthusiastic commissioning of services that look superficially similar to each other and to a model reported as cost-effective, when in fact either at the time or over a period after commissioning there are differences in staffing or referral patterns that invalidate the original commissioning assumptions. An important function is served by studies that describe what patient groups actually receive—what sort of service and in what numbers.

This research is thus timely in exploring methods to evaluate the function and performance of liaison psychiatry services.

There are, however, challenges in conducting such research.

First, defining exposure to liaison psychiatry is difficult because there is substantial heterogeneity in the composition, purpose and size of liaison psychiatry services. For example, a recent survey conducted in England^25^ found that just over half of the services provided a 24-hour 7-day service and only one-third ran specialist outpatient clinics. Most of the services provided cover of acute hospital wards and emergency department (ED) and nearly all services were multidisciplinary, but staff mix varied such that about one-third employed less than one full-time equivalent of a consultant in psychiatry. Only one-third of services had separate teams for older adults and adults of working age. These differences were not fully explained by variation in acute hospital characteristics. Also, the mechanism by which liaison psychiatry services might produce improved patient and organisational outcomes is unclear—for example, with some suggesting that the main benefit is by securing rapid discharge to community-based services, while others emphasise the specialist nature of shared inpatient management or of outpatient clinics provided by the service.

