Patient care pathways for patients attending hospitals using liaison psychiatry services in each configuration will be constructed to provide a view of health and healthcare across both primary and secondary care. Pathways will be constructed for patients for a period of 12 months following their index (first) hospital admission in the index period. The cost of each pathway to the healthcare sector will then be calculated using national data sources (see below). We will adopt a whole system perspective in order to determine if there is an association between the configuration of liaison psychiatry services and healthcare utilisation by patients. Metrics including emergency admissions, occupied bed days and length of stay will be analysed by age band.

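### The cost-effectiveness analysis is given two different perspectives, and the named data sources do not reach as far as the whole-system label

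*Protocol article*

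**What the plan says.** The protocol article describes the economic perspective in three places.

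- **Abstract, Methods and analysis:** "We will carry out an exploratory incremental cost-effectiveness analysis from a whole system perspective".
- **Methods and analysis, Data extraction:** "We will adopt a whole system perspective in order to determine if there is an association between the configuration of liaison psychiatry services" and healthcare use. The same paragraph sets the cost boundary: "The cost of each pathway to the healthcare sector will then be calculated using national data sources".
- **Methods and analysis, Data analysis:** as an example of what can be fixed beforehand, "the perspective of the economic evaluation which will be the health service provider and the comparator which will be usual care".

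The cost variable itself, also under Data analysis, is the "total costs of any identified healthcare utilisation derived from factors such as inpatient days, readmission rates, ED attendances and GP visits", valued from national unit costs. There is a fallback: "Where these are not available, local costs will be assigned".

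Utilisation comes from three sources (Abstract and Data sources): Hospital Episode Statistics for emergency department, inpatient and outpatient episodes; ResearchOne for primary care at participating SystmOne practices; and mental health trust databases, described as holding care given by liaison psychiatry services. On mechanism, the Introduction reports that some hold that "the main benefit is by securing rapid discharge to community-based services".

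**The concern.** The perspective decides which costs enter the numerator of a cost-effectiveness ratio. Here one analysis carries two labels, and the reader cannot tell which sectors the result is meant to cover.

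The gap between label and data matters more than the wording. If liaison contact shortens stays partly by moving patients into community services, the saved bed days are recorded, while some of the care that replaces them may fall in sectors for which no data source is named. A result presented as whole-system would then lean towards finding savings. The study was set up to confirm or refute striking savings claims and is addressed to commissioners, so an error in that direction bears on its main message.

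**Working it through.** The document gives no figure to reproduce. The check is a comparison of the text, followed by the direction of the bias.

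**Step 1. Do the statements concern the same analysis?** The Abstract attaches the whole-system label directly to the exploratory incremental cost-effectiveness analysis. The Data analysis section introduces exploratory incremental cost-effectiveness analyses and then gives the provider as their perspective. These are the same item, so the two statements conflict. The Data extraction sentence is less clear: it attaches the label to an association between service configuration and healthcare use, which can be read as a separate utilisation analysis. The conflict therefore rests on the Abstract against Data analysis, with Data extraction adding a third term, the healthcare sector.

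**Step 2. Which sectors have a named utilisation source?**

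| Sector | Named source |
|---|---|
| Emergency department, inpatient, outpatient | Hospital Episode Statistics |
| Primary care | ResearchOne, linked patients only |
| Liaison psychiatry contacts | Mental health trust databases |
| Community mental health care outside liaison | None named |
| Social care | None named (a health and social care unit-cost source is cited, but no source of use) |

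**Step 3. Do the sources fit either label?** They are narrower than a whole system, because the last two rows are empty. They are wider than an acute hospital provider, because GP visits are costed. If the provider means the NHS as a whole, non-liaison community mental health care is still without a named source.

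**Step 4. Direction of the bias.** Let X be the fall in measured cost over the 12-month pathway, already net of any rise in GP, outpatient, emergency department or readmission cost in linked patients. Let unmeasured cost rise by r × X.

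- Reported saving = X
- Whole-system saving = X − rX = X(1 − r)

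The document does not give r. As an assumed range:

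| r | Whole-system saving as a share of the reported saving |
|---|---|
| 0 | 100% |
| 0.25 | 75% |
| 0.5 | 50% |
| 1 | 0% |
| 1.2 | −20% (a net cost) |

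Any r above 0 means that the reported saving is too large as a whole-system figure. The table shows the form of the dependence and is not an estimate.

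**The case against.** The strongest reply is that this is loose terminology. Only one dependent variable is described, pathways are said to span primary and secondary care, and the provider could mean the NHS as a whole. The three labels might then stand for one cost set. The list of cost items is illustrative, the article condenses a fuller protocol, and Data analysis says that capturing how general hospital, general mental health and liaison services interact is a key task for the model. The analysis is called exploratory, follows NICE methods guidance and includes sensitivity analyses.

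Much of this stands. The article does not show two rival cost totals, and a fuller protocol may name more sources. But the perspective is offered as something already specified, so the conflict is not a detail left for later. The intention to capture how services interact names no source of community use, and the general promise of sensitivity analyses does not mention shifted cost.

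A reader might also infer several stronger points that the document does not support:

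- **That all replacement care goes uncounted.** It does not: readmissions, emergency department attendances and GP visits are costed, and outpatient episodes are in the hospital data. Only non-liaison community mental health care and social care are in doubt.
- **That missing liaison records at hospitals without a service bias the costs.** Patients there have no liaison contact to cost.
- **That the local-cost fallback turns site price differences into configuration effects.** The text does not say that each site keeps its own price, and the main items are to be valued from national sources.
- **That a given percentage of the saving is false.** Any such figure rests on an assumed r.

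**Conclusion.** The point holds in limited form. The Abstract and the Data analysis section give the same cost-effectiveness analysis different perspectives, and the whole-system label claims a breadth that the named sources do not deliver. Since discharge to community services is among the suggested mechanisms, the gap lies on a plausible route from liaison contact to lower hospital cost, and any cost shifted to the unmeasured sectors would inflate the apparent whole-system saving.

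The contradiction can be read directly from the text. The data gap assumes that the three named sources are the complete set. The bias further assumes that liaison contact raises use in the unmeasured sectors (r > 0). Its size cannot be derived from the document. The conclusion affects what the result may be said to show, and does not make the hospital and primary care cost comparison invalid in its own terms.

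**What to change.** 1. State one perspective in the Abstract, Data extraction and Data analysis, defined by the sectors actually measured: NHS hospital care, primary care and the liaison service. Drop the whole-system label unless a utilisation source is named for each further sector.
2. Declare community mental health care outside liaison and social care as unmeasured.
3. Add a sensitivity analysis on shifted cost. With B bed days saved and an assumed unmeasured community cost c per bed day saved, the adjusted saving is X − cB. Show it over a range of c and report the break-even value c = X / B at which the saving disappears.
4. As a minor clarification, state that where local costs are used, one common unit cost per item applies at every site.

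The cost is some rewording, one extra analysis that needs no new data, and a narrower claim.
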